One of the most important factors influencing the effectiveness of iTBS is the stimulus dose (Volz et al., 2013; Chung et al., 2016). When studying stroke patients, most researcher used a block of 600 iTBS pulses (Ackerley et al., 2014, 2016; Watanabe et al., 2018; Chen et al., 2019; Ding et al., 2021) and a few used two blocks of 600 pulses iTBS (Hsu et al., 2013; Chen et al., 2021). Previous studies in healthy human subjects suggested that iTBS might dose-dependently modulate neural plasticity, i.e., the higher the dose of iTBS, the greater the changes in neural plasticity induced (Nettekoven et al., 2014; Yu et al., 2020). Nettekoven et al. (2014) applied three blocks of 600 pulses iTBS to motor cortex and found that the cortical excitability enhancement effect was significantly greater than two blocks of 600 pulses iTBS and one block of 600 pulses iTBS. They also found that functional connectivity between M1 and ipsilateral dorsal premotor cortex continued to increase in a dose-dependent manner after 1,800 pulses of iTBS over M1. However, studies in healthy human subjects are insufficient to support the clinical application of iTBS. Other studies revealed that in patients with neurological disorders, high doses of rTMS produced stronger and longer lasting therapeutic responses than low doses (Nyffeler et al., 2009; Williams et al., 2018), but an agreement on how to select the best dose of iTBS for stroke patients with upper limb motor dysfunction is limited until now. There is a lack of studies comparing the difference in efficacy of different doses of iTBS for upper limb motor dysfunction in stroke patients.

Therefore, the objectives of this randomized controlled clinical trial are: (1) to investigate the safety and efficacy of one block of iTBS (600 pulses-iTBS), two blocks of iTBS (1,200 pulses-iTBS), or three blocks of iTBS (1,800 pulses-iTBS) in the treatment of upper limb motor dysfunction in stroke patients; (2) to compare the efficacy of three doses of iTBS; (3) to explore the neural mechanism of upper limb motor recovery after stroke using resting-state functional magnetic resonance imaging (rs-fMRI). Our hypothesis is that the higher the dose of iTBS, the greater the improvement in upper limb motor function in stroke patients. This study may provide new insights into the efficacy and underlying neuroplastic mechanisms of iTBS for treating poststroke upper limb motor dysfunction.

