### Outcome measures

2.6.

The Fugl-Meyer Assessment of the Upper Extremity (FMA-UE) score from baseline (T0) to end of intervention (T1) is defined as the primary outcome. The FMA-UE is a standardized scale of upper limb motor impairment ranging from 0 to a maximum of 66 points (Fugl-Meyer et al., 1975; Chen Y. F. et al., 2022). Secondary outcomes are the Wolf Motor Function Test (WMFT), Grip Strength (GS), MAS, Modified Barthel Index (MBI), and Stroke Impact Scale (SIS). The WMFT consists of 15 tasks, each of which must be completed in at least 120 s, and the performance on each task is scored on a six-point scale (0–5) (Morris et al., 2001; Wolf et al., 2001). The GS is measured with a grip dynamometer. During the measurement, the patient’s shoulder joint is abducted to 90°, the elbow joint is flexed to 90°, and the forearm is placed on the table. The patient is instructed to hold the grip dynamometer as hard as possible (Bertrand et al., 2015). The grip dynamometer automatically records the highest value. A total of 3 measurements are taken with a 1-min rest interval between each measurement. The MAS is commonly used to assess spasticity. The MAS scores for the shoulder, elbow, wrist, and fingers of the affected upper extremity will be recorded. The MBI is used to assess the patient’s ability to perform activities of daily living (ADL), including 10 items out of 100 points (Ohura et al., 2017). The SIS is one of the commonly used scales to evaluate the quality of life of stroke patients, which consists of eight items, and each item has a full score of 100 points (Mulder and Nijland, 2016), and we will take the average score of the eight items as the outcome. Each participant will undergo the following clinical assessments pre-treatment (T0), post-treatment (T1), and at the 3-weeks follow-up (T2): FMA-UE, MBI, SIS. The following clinical assessments will be performed only before and after treatment: WMFT, GS, MAS. We will also perform exploratory analyses based on the rs-fMRI data collected before and after the treatment.

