The magnetic resonance imaging (MRI) data will be collected by using a Philips Ingenia 3.0 T Magnetic Resonance System at the China Rehabilitation Research Center. Three rs-fMRI sessions of 8 min 6 s each are acquired using a gradient echo planar imaging sequence with the following parameters: TR = 2,000 ms, TE = 30 ms, FOV = 224 × 224 mm^2^, Flip angle = 90°, matrix = 64 × 64, Slice number = 32, voxel size = 3.5 × 3.5 × 4.35 mm^3^. Anatomical images are acquired using a high-resolution T1-weighted sequence (TR = 7.13 ms, TE = 3.22 ms, Flip angle = 7°, 192 slices, FOV = 256 × 256 mm^2^, Matrix = 256 × 256, voxel size = 1 × 1 × 1 mm^3^).

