### Data analysis

2.7.

We will use SPSS version 25 for statistical analysis. Analysis of variance (continuous and ordinal data) or χ^2^ tests (categorical data) will be used to compare demographic and baseline characteristics. A mixed-design ANOVA (between-subjects factor: group; within-subjects factor: time; and time-by-group interaction) will be used to detect any significant differences in the change of outcomes. Any factor with a significant difference between the groups at the baseline will be included as a covariate in the ANOVAs. If a significant time-by-group interaction effect is found, comparisons using pairwise *t*-tests will be performed by separately comparing the changes from baseline. Bonferroni correction is applied for *post hoc* tests. Before entering the data into the ANOVAs, the Shapiro–Wilk test will be used to test whether the data are normally distributed. For non-normally distributed measures, the non-parametric Kruskal-Wallis H test is performed to compare across conditions. The level of significance is defined as *p* < 0.05 (2-tailed). For missing data, intention-to-treat (ITT) analysis is used (Matilde Sanchez and Chen, 2006).

The pre-processing of the MRI data will be in accordance with the previously described pipeline (Yeo et al., 2011). After preprocessing, regional homogeneity (ReHo), degree centrality (DC), amplitude of low frequency fluctuations (ALFF), and seed-to-voxel analyses will be performed to measure functional connectivity within motor networks. ReHo is calculated based on the Kendall’s concordance coefficient, which is used to measure the time-series synchronization between a given voxel and neighboring voxels, with higher values representing better concordance between the local voxel and the regional brain activities. In network analysis, DC is the most direct measure of node centrality. A higher degree of a node means that the node has a higher DC and the node is more important in the network. The ALFF value is related to the strength of local neural activity. It is often used to measure the BOLD signal in the frequency range of 0.01–0.1 Hz (Zang et al., 2004). Differences between conditions are considered significant if *p* < 0.05 at the voxel level. A false discovery rate (FDR) cluster corrected *p* < 0.05 is applied.

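### The rs-fMRI rule forms clusters at voxel p < 0.05, which makes its 5% error rate fragile if cluster p-values are parametric and its localisation coarse under any method

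*Protocol article*

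**What the plan says.** The second paragraph of section 2.7 (Data analysis) lists four families of imaging measure: "regional homogeneity (ReHo), degree centrality (DC), amplitude of low frequency fluctuations (ALFF), and seed-to-voxel analyses will be performed". The decision rule follows in two sentences: "Differences between conditions are considered significant if *p* < 0.05 at the voxel level", then "A false discovery rate (FDR) cluster corrected *p* < 0.05 is applied". The section's general significance level is two-tailed 0.05; it is not repeated for imaging.

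The imaging serves the third objective in the Introduction, "to explore the neural mechanism of upper limb motor recovery after stroke". Section 2.6 (Outcome measures) fixes its status: "We will also perform exploratory analyses based on the rs-fMRI data collected before and after the treatment". The Discussion adds a hypothesis that iTBS works through connectivity in the motor network.

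**The concern.** Cluster inference has two steps. A voxel threshold decides which voxels join into clusters, and a second test asks whether a cluster is larger than chance would produce. The first step is set here at p < 0.05 with no voxel-level correction stated.

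Two things follow from so low a threshold. First, parametric cluster p-values rest on an approximation that works best at high thresholds and with Gaussian-shaped spatial correlation. At a low threshold, departures from that shape can make cluster p-values too small. Second, many voxels pass by chance and join together, so a cluster has to be large before it counts. A significant cluster shows only that there is signal somewhere inside it, so a large cluster says little about where.

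At stake is how far a cluster reported as corrected at 0.05 can be trusted, and placed, when it is used to argue a motor-network mechanism. This is a threshold that the article states, not a detail that it leaves out.

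**Working it through.** **What cannot be reproduced.** The plan's figure is the nominal 0.05. The achieved rate cannot be derived from the article, because smoothing, spatial autocorrelation, search mask and cluster-inference method are not given. An article may leave these to the full protocol, so they are treated as assumptions here.

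**Inputs from the protocol article**
- Voxel p < 0.05, cluster FDR 0.05, two-tailed level (section 2.7).
- Grid of 64 × 64 × 32 voxels of 3.5 × 3.5 × 4.35 mm (section 2.6), so one voxel is 53.29 mm³.
- 14 participants per group (section 2.3).

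**Assumed inputs**
- Ellipsoid brain mask of 26,032 voxels: 26,032 × 53.29 mm³ = 1.39 L.
- Parametric (Gaussian random field) cluster-extent p-values, with Benjamini-Hochberg FDR over clusters.
- Noise (a): Gaussian spatial correlation, FWHM 8 mm.
- Noise (b): long-tailed correlation, 70% of variance at 8 mm and 30% at 20 mm.

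**Step 1: chance voxels.** 0.05 × 26,032 ≈ 1,302 voxels pass p < 0.05 in a null map. At p < 0.001 about 26 pass.

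**Step 2: false clusters under the null.** With no true effect every significant cluster is false, so FDR control at 5% means at most a 5% chance of any significant cluster. From 200 simulated null comparisons of 14 v 14 per scenario:

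| Voxel threshold (two-tailed) | (a) Gaussian | (b) Long-tailed |
|---|---|---|
| p < 0.05 | 7.0% | 34.5% |
| p < 0.01 | 1.5% | 11.0% |
| p < 0.001 | 4.0% | 6.5% |

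The Monte Carlo standard error is √(q(1 − q)/200). It is 1.8 points at 7.0%, 3.4 at 34.5%, 1.4 at 4.0% and 1.7 at 6.5%. So 7.0% is within simulation error of 5%, and 34.5% is not. If the voxel threshold were one-tailed at 0.05, the figures in the first row would be 16.0% and 49.5%.

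**Step 3: cluster size needed.** For search volume V in voxels, smoothness F in voxels and threshold u:
- E[N] = V(1 − Φ(u))
- E[m] = V (4 ln 2)^1.5 / (F₁F₂F₃) × (2π)^−2 × (u² − 1) × exp(−u²/2)
- β = (Γ(2.5) E[m] / E[N])^(2/3)
- family-wise p of a cluster of k voxels = 1 − exp(−E[m] exp(−β k^(2/3)))

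Set this p to 0.025 per tail and solve for k. In scenario (a) the estimated smoothness gives F₁F₂F₃ = 9.08.
- At p < 0.05, u = 1.960: E[N] = 650.8, E[m] = 139.6, β = 0.433, so k = 88.7, rounded up to 89 voxels = 4.7 mL.
- At p < 0.001, u = 3.291: E[N] = 13.0, E[m] = 14.7, β = 1.310, so k = 10.7, rounded up to 11 voxels = 0.6 mL.

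In scenario (b), F₁F₂F₃ = 14.72, and the same steps give 132 voxels (7.0 mL) and 16 voxels (0.9 mL). The ratio is about eight in both scenarios (89/11 = 8.1; 132/16 = 8.3).

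**Step 4: does permutation change the size?** The median largest null cluster was 52 voxels (2.8 mL) in (a) and 113 voxels (6.0 mL) in (b) at p < 0.05. At p < 0.001 it was 4 and 5 voxels (0.2 and 0.3 mL). A family-wise permutation cut-off lies in the upper tail of that distribution, so it exceeds these medians. Clusters must therefore still be large. Under FDR the cut-off depends on the data and can be lower when several clusters carry signal, so these sizes are a guide.

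**The case against.** The strongest reply is that parametric inference is assumed. The article names no method, and permutation-based cluster p-values would hold the error rate at any forming threshold. That stands, and it makes the error-rate part of the point conditional.

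The size of any inflation also rests on a noise model that no document supplies. With Gaussian smoothness and two-tailed testing, the stated rule came out within simulation error of 5%. A search restricted to a motor mask would change the volume and the figures again.

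The article already calls the imaging analyses exploratory, and the rule touches no clinical outcome. That stands too and limits the weight of the point. It does not remove it, since the article still describes the results as significant and corrected.

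Three stronger readings are tempting, and the documents support none of them.
- A reader might infer that false mechanism findings are likely, or that 5% control certainly fails. That would need the inference method and the spatial correlation, and neither is given.
- A reader might infer that clusters could not be assigned to any motor region. No region volumes are given to compare; only coarser localisation follows.
- A reader might infer that four measures multiply the error. If each held 5% and they were independent, the chance of any false finding would be 1 − 0.95⁴ = 18.5%. But the measures come from the same scans and are probably correlated, so this is not an estimate for the trial.

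**Conclusion.** The point holds in a limited form. On the natural reading of section 2.7, clusters are formed at an uncorrected voxel p < 0.05, which is a poor choice of threshold.

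- **Error rate, conditional on parametric cluster p-values:** validity depends heavily on the shape of the spatial correlation (7.0% to 34.5% across the two assumed noise models). At p < 0.001 it depends on it far less (4.0% to 6.5%).
- **Localisation, under parametric or permutation inference:** a surviving cluster must be roughly eight times as large as at p < 0.001, by the parametric cut-off (4.7 to 7.0 mL against 0.6 to 0.9 mL).

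These figures rest on the assumed mask, on 14 per group with no dropout, and on the two noise models. They show how sensitive the rule is, not the error rate that this trial will have. The consequence is confined to the exploratory mechanism objective. The FMA-UE analysis, the secondary clinical outcomes and the sample size are unaffected. This is a cheap improvement, not a fault that threatens the trial.

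**What to change.** Replace the two-sentence rule in section 2.7 with one that specifies:
- a two-tailed cluster-forming threshold of p < 0.001;
- cluster-level correction at 0.05, preferably by permutation, with the method named;
- application to the group-by-time contrast of each map.

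Keep the exploratory status already given in section 2.6; no new label is needed. It would also help to say in a phrase how results across the four measures will be read together.

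The change needs no extra patients or scans and uses standard software. It should be made before the imaging data are analysed. The cost is some loss of sensitivity to weak, spatially diffuse effects.

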### Safety

2.8.

Any adverse effects occurring during MRI scan will be reported within 24 h. Participants will be provided with earplugs to protect their hearing from noise. iTBS treatment may cause headaches, scalp sensations or nociception, dizziness, or fatigue in some patients, which may resolve on their own after stimulation stops without special treatment. In particular, seizures, which are the most serious TMS-related adverse effect with a risk of about 0.02%, are expected to occur only during or immediately after stimulation (Rossi et al., 2009). To minimize the risk of adverse events, participants will be screened strictly according to the inclusion and exclusion criteria. There will be a record of all adverse events and a comparison of the incidence of adverse events between groups. In addition, serious adverse events will be reported to the ethics committee immediately upon occurrence.

## Discussion

3.

This randomized controlled clinical trial aims to investigate and compare the efficacy of three doses of iTBS on the recovery of upper limb motor function in stroke patients. Furthermore, we hope to provide a theoretical basis for clinical application by investigating the neural effects of iTBS intervention on upper limb motor dysfunction. Our results may provide supportive evidence for the optimal dose of excitatory iTBS intervention in the treatment of upper limb motor dysfunction after stroke.

In this study, we hypothesize that iTBS can promote upper limb motor recovery in stroke patients by modulating functional connectivity within the motor network. We also hypothesize that the higher the stimulus dose, the greater the improvement in motor function. The following evidence supports this hypothesis. Increasingly, it is thought that increasing the dose of rehabilitation may lead to better motor function outcomes in stroke patients (Cooke et al., 2010; Lang et al., 2015; Winstein et al., 2019). rTMS is an important physiotherapeutic approach, and its use in rehabilitation is inseparable from the choice of parameters, with the stimulus dose being of particular importance. and rTMS has gained attention in recent years as a promising physical therapy approach. iTBS is a type of rTMS that has great potential in the treatment of post-stroke motor dysfunction and has attracted much attention in recent years. Previous studies on healthy subjects have found that iTBS with more stimulus pulses more significantly enhances motor cortex excitability and functional connectivity within the motor network. However, studies comparing the effects of different doses of iTBS on upper limb motor recovery in stroke patients are lacking, and our study will fill this gap.

In terms of experiment design, our study raises some methodological concerns worth discussing. We set up four groups (Group A, Group B, Group C, and Group D) corresponding to four conditions (600 pulses active iTBS, 1,200 pulses active iTBS, 1,800 pulses active iTBS and 1,800 pulses sham iTBS) in this study. It is important to note that, for statistical reasons, the iTBS intervention protocol for both Groups A and B includes sham stimulation so that the total stimulation time per day is the same for each group, thus ensuring successful blinding. Referring to a previous similar study (Blumberger et al., 2021), and considering that patients will receive conventional rehabilitation training after iTBS intervention, we place the sham stimulation before the active stimulation in Groups A and B in order to ensure that the time interval between the last active stimulation and the conventional rehabilitation training is the same for each patient per day. In this study, block randomization is used to balance the effect of enrollment time on patients’ baseline characteristics (Lim and In, 2019). Also, outcome will be evaluated at pre-intervention, the end of first, second, and third week of post-intervention. Taking into account the length of the patient’s stay, we are going to conduct a three-week intervention with the patient. Additionally, to observe the short-term and long-term effects of iTBS, clinical outcomes will be evaluated before, after, and during the third week after the intervention.

M1 plays an important role in motor recovery after stroke. The researchers examined the brain activation during movement of the upper limb in stroke patients and described the altered activity in the ipsilateral and contralateral M1 (Rehme et al., 2012; Favre et al., 2014; Hannanu et al., 2017; Braaß et al., 2023). Previous studies have suggested that the activity of the ipsilateral M1 may be reduced and the activity of the contralateral M1 may be increased after stroke (Calautti et al., 2007, 2010; Larivière et al., 2018). Thus, non-invasive brain stimulation may be applied to modulate stroke-induced changes of motor network activity and connectivity to improve motor function (Grefkes and Fink, 2012; Tang et al., 2015). On the basis of the interhemispheric inhibition (IHI) model (Di Pino et al., 2014), excitatory stimulation applied to the ipsilateral hemisphere or inhibitory stimulation applied to the contralateral hemisphere may produce a consistent effect on functional recovery. In the present study protocol, based on baseline rs-fMRI data, we will delineate 18 functional networks for each patient, and the excitatory iTBS intervention will target M1 in the ipsilateral upper extremity sensorimotor network.

fMRI, a non-invasive brain imaging technique with high spatial resolution, has been widely used to explore the brain. Some previous studies have used fMRI to investigate the neural mechanisms by which low-frequency rTMS or high-frequency rTMS improves motor recovery after stroke (Grefkes et al., 2010; Li et al., 2016; Du et al., 2019; Guo et al., 2021; Chen Q. et al., 2022; Juan et al., 2022), but few studies have used fMRI to investigate the potential effects of iTBS on motor function after stroke. Volz et al. (2016) found that the addition of iTBS to prime physiotherapy in recovering stroke patients seemed to interfere with motor network degradation. Therefore, our study will use rs-fMRI to explore potential therapeutic mechanisms for iTBS. Although task-state fMRI can reflect brain activity during the performance of specific tasks, given that the subjects are patients with post-stroke motor dysfunction, the quality of the tasks performed by the patients may vary widely, which could affect the results, so we chose rs-fMRI.

iTBS has the advantages of easy operation and short stimulation time, and its efficacy may be influenced by the stimulus dose. We hope that our protocol and results can elucidate this potential effect and provide guidance for the treatment of patients with upper limb motor dysfunction after stroke.

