## Introduction

1.

Motor dysfunction of the upper limb occurs in 73–88% of first-ever stroke survivors, and 55–75% of patients suffer residual motor dysfunction of the upper limb 3 to 6 months after stroke onset (Lawrence et al., 2001). Stroke patients with upper limb motor dysfunction often have limited independence in daily activities and reduced quality of life (Faria-Fortini et al., 2011). Therefore, improving upper limb function is an important goal of stroke rehabilitation (Pollock et al., 2014; Veerbeek et al., 2017). To date, conventional rehabilitation training remains the primary treatment for upper limb motor dysfunction after stroke, but effectiveness is limited. It is necessary to develop other therapeutic methods to improve the effectiveness of conventional rehabilitation training for upper limb motor dysfunction after stroke (Barreca et al., 2003; Coscia et al., 2019).

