### Study design

2.1.

This is a prospective, single-center, randomized, parallel, sham-controlled clinical trial. This study will be conducted at Beijing Bo’ai Hospital, China Rehabilitation Research Center (Beijing, China). Hospitalized patients will be screened in accordance with strict inclusion and exclusion criteria. After written informed consent is obtained, demographic information collection and baseline assessments are scheduled for each patient. All participants will be randomly assigned with a ratio of 1:1:1:1 to one of the following four groups: Group A, Group B, Group C, and Group D. Details of the study design and data collection are presented in Figure 1 and Table 1. Behavioral assessments will be performed at baseline (T0), at the end of the iTBS intervention (T1), and 3 weeks post-treatment (T2) to assess upper limb motor function, activities of daily living (ADLs) performance, and quality of life. In addition, rs-fMRI data will be collected before and after the end of the intervention. This study has been approved by the Medical Ethics Committee of China Rehabilitation Research Center (No.: 2022-149-01) and registered on www.chictr.org.cn under the registration number ChiCTR2300068177.

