#### Inclusion criteria

2.2.1.

Participants are considered eligible if they meet the following criteria: (1) have a unilateral ischemic or hemorrhagic subcortical stroke; (2) first or previous stroke without residual disability (modified Rankin Scale ≤1 before this onset); (3) 1–6 months post-stroke; (4) are 35–75 years old; (5) presented with a unilateral upper limb motor dysfunction with a Brunnstrom stage score between 2 and 5 in the upper limb or hand; (6) can sign an informed consent form.

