### Sample size

2.3.

According to a previously published meta-analysis comparing iTBS and sham stimulation (Zhang et al., 2017), the expected effect size Cohen’s d for the comparison of the two groups was 0.6, and the effect size (f) for the comparison of the corresponding four groups was approximately 0.3. Using G*Power v3.1.9.2, the estimated sample size required for a 4-group design with a ratio of 1:1:1:1, given a power of 0.95 and a 2-tailed alpha error probability of 0.05, is 44 patients in total. Considering a dropout rate of 20%, at least 14 participants are needed for each group. Therefore, 56 patients will be enrolled in this study.

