### Randomization and blinding

2.4.

Block randomization method will be used in this study. Once informed consent and baseline data have been obtained, all eligible participants will be randomly assigned to four groups using a random number sequence generated by SPSS 25.0 software. Random assignment is carried out by an independent researcher and kept in a sealed opaque envelope. The researchers responsible for iTBS will not be involved in the study design, recruitment, randomization, assessment, or data analysis. Participants and other researchers (such as outcome assessors or statisticians) will be blinded to the group allocation.

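### Time since stroke (1–6 months) is neither balanced by the allocation nor always adjusted for; the significance-triggered covariate rule would usually miss a chance imbalance, at a modest cost in precision

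*Protocol article*

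**What the plan says.** The Protocol article admits patients under inclusion criterion "3) 1–6 months post-stroke" (section 2.2.1). On allocation, section 2.1 states "All participants will be randomly assigned with a ratio of 1:1:1:1 to one of the following four groups" and section 2.4 states "Block randomization method will be used in this study". No stratification factor is named. The Discussion explains the choice: "block randomization is used to balance the effect of enrollment time on patients’ baseline characteristics".

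Section 2.3 sets 14 patients per arm, from 44 evaluable patients (11 per arm) and 20% dropout. The primary outcome (section 2.6) is FMA-UE from T0 to T1, about three weeks. Section 2.7 makes a factor a covariate in the ANOVA only if the groups differ significantly on it at baseline. Time since stroke is not named as a covariate.

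**The concern.** Time since stroke is a plausible predictor of how much FMA-UE changes over three weeks without iTBS. It is known for every patient before allocation, because eligibility depends on it. If one arm happens to receive more early patients, its mean change moves for a reason unrelated to dose. The sham arm removes average spontaneous recovery, but not a difference in case mix between arms.

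The trial sets out to rank three active doses with small arms, so avoidable noise in the arm means matters. A covariate that enters only after a significant baseline test is a poor guard: with 14 per arm such a test has little power, and prognostic relevance does not depend on significance.

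**Working it through.** **Arm size.** Section 2.3 gives "the effect size (f) for the comparison of the corresponding four groups was approximately 0.3" and "given a power of 0.95 and a 2-tailed alpha error probability of 0.05, is 44 patients in total". The total of 44 reproduces as a group-by-time interaction with 4 groups, 3 time points and correlation 0.5 (assumed): power 0.961. Then 11/(1 − 0.20) = 13.75, so 14 per arm and 56 in all. (With the two time points of the primary outcome, the same inputs give 52 evaluable. That is a separate matter.) The checks below use 14 per arm, and 11 where stated.

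**Chance imbalance in time since stroke.** Assumption: entry times uniform on 1 to 6 months, as the documents give no distribution.
- SD of one patient's time = (6 − 1)/√12 = 1.443 months.
- SD of the difference between two arm means = 1.443 × √(2/14) = 0.55 month; with 11 per arm, 0.62.
- Expected gap between the extreme two of four arms = 2.059 × 1.443/√14 = 0.79 month; with 11 per arm, 0.90.
- Simulation: a gap of 1 month or more in about 26% of trials with 14 per arm (blocks of 4, assumed), and about 37% with 11 per arm (simple allocation).

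**The covariate rule.** Allocation is random, so a baseline test at 0.05 is significant in about 5% of trials whatever the factor. Simulation confirms about 5%. Among trials with a gap of 1 month or more, the test is not significant in about 80%.

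**Possible size in FMA-UE points.** The documents give no recovery curve. Assumption: three-week spontaneous gain falls exponentially from entry at 1 month to entry at 6 months. The shift is the largest arm-to-arm difference due to this imbalance alone, with unstratified blocks of 4.

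| Assumed gain, 1 → 6 months | Mean shift | Shift ≥ 1 point | Shift ≥ 2 points |
|---|---|---|---|
| 6 → 1 | 0.8 | 24% | 0.1% |
| 8 → 2 | 0.9 | 41% | 1% |
| 10 → 2 | 1.2 | 65% | 9% |

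Stratifying at 3 months lowers the mean shift to about 0.4, 0.5 and 0.6 point. Shifts of 1 point or more then occur in about 0.1%, 1% and 11% of trials, and gaps of 1 month or more in under 0.5%.

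**Scale.** The SD of FMA-UE change is not given; take 5 to 10 points (assumed). Section 2.3 states "the expected effect size Cohen’s d for the comparison of the two groups was 0.6", so the planned active-versus-sham effect is 0.6 × 5 = 3.0 to 0.6 × 10 = 6.0 points. Ordinary sampling noise among four arms of 14 gives an average largest gap of 2.059 × SD/√14, which is 2.75 to 5.5 points. On these curves time since stroke explains about 2% to 20% of the variance in change.

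**Error rate and precision.** In simulated trials with no dose effect, a one-way ANOVA on change has type I error of about 0.05 overall. Given a gap above 1 month it is 0.066, 0.083 or 0.104 if time since stroke explains 10%, 20% or 30% of the variance (R²). Always adjusting multiplies the standardised effect by 1/√(1 − R²). For one pair of arms with 14 each, d = 0.6 and alpha 0.05 without multiplicity correction, power rises from 0.35 to 0.37 (R² = 0.05), 0.39 (0.1) or 0.43 (0.2).

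**The case against.** The strongest reply is that this is chance, not bias. The standard error already contains the variation, unconditional type I error is near 5%, and leaving a small single-centre trial unstratified is legitimate. All of that stands. It limits the point to precision and to the estimate in the trial actually run.

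Four stronger readings are tempting, and the documents do not support them.

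- A reader might infer that the Discussion wrongly credits blocking with balancing baseline characteristics in general. It claims only balance over enrolment time, which is what blocking provides. That sentence needs no correction.
- A reader might take the Introduction as proof of recovery inside the entry window. It reports dysfunction in 73–88% of first-ever stroke survivors and then "55–75% of patients suffer residual motor dysfunction of the upper limb 3 to 6 months after stroke onset". These are overlapping prevalence ranges, not FMA-UE gains, and any fall could have come before month 1.
- A reader might infer that the imbalance alone could pass for, or conceal, a dose effect. On the assumed curves a shift of 2 points or more is rare to uncommon (0.1% to 9% of trials), against a planned effect of 3.0 to 6.0 points and sampling noise that is usually larger.
- A reader might say the imbalance is left wholly unhandled. Section 2.7 does have a rule; it is weak rather than absent.

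A further objection is that baseline severity might be a better stratifier and that the 3-month cut is arbitrary. That is fair. It is why covariate adjustment is the main remedy and stratification the optional one.

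**Conclusion.** The concern holds in a limited form. A chance imbalance in time since stroke of 1 month or more between some two arms is expected in about a quarter of trials of this design, and the rule in section 2.7 would leave about four in five of these unadjusted. The validity of the randomisation and the overall error rate are not in question.

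What is lost is a modest amount of precision in comparisons that have little to spare. The percentages rest on uniform entry times. The point shifts rest on assumed recovery curves, and the variance shares also on an assumed SD of 5 to 10. The documents support none of these sizes directly. Always adjusting is nonetheless better than the significance-triggered rule, because it does not depend on a test that seldom fires and costs almost nothing. It is a recommended improvement, not a fatal flaw.

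**What to change.** In section 2.7, exempt time since stroke from the significance-triggered rule and name it as a pre-specified covariate in the FMA-UE analysis, whatever the baseline tests show. In the mixed ANOVA it must enter with its interaction with time, since otherwise it cannot adjust the comparison of changes. The pairwise follow-up comparisons should use the adjusted changes.

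If enrolment has not started, also amend section 2.4 to block-randomise 1:1:1:1 within two time-since-stroke strata (for example 1 to <3 and 3–6 months), with separate sealed envelopes per stratum, and keep the stratum in the model. If enrolment has begun, make the covariate change alone, before unblinding.

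Cost: one or two degrees of freedom, a second envelope list if stratified, and arm sizes that may differ by one or two patients because of incomplete last blocks. The planned 56 patients and the visit schedule are unchanged.
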